**Implementation Quality**		
Adherence	Degree of fidelity to the content of the BA sessions	Supervision Ratings
Quality	General quality implementing the BA sessions	Supervision Ratings
Depression Care Competence	Depression care competence rated by supervisors	Provider Competency Assessment
Treatment Completion	# and % of clients with 4 or more sessions	Session Progress Note
Treatment Dropout	# and % of clients with 1 or less sessions	Session Progress Note
**Effectiveness**	Pre- and post-treatment differences; PHQ-9 Survey data	PHQ-9 Treatment Data and Survey Data
Client Improvement	50% reduction in PHQ-9 score	PHQ-9 – Session Scores (first and last)
Client Remission	Last PHQ-9 < 5	PHQ-9 – Session Score (last)
**Maintenance**	Independent implementation is considered an early sign of maintenance or penetration	Active Implementation Support; Transitional Support

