**Fig. 2 Fig2:**
[figure not shown]
Process indicator diagram *BA: Behavioral activation; Rx: Treatment; PHQ-9: Patient Health Questionnaire with 9 items*

According to the stepped-care treatment model, mild to moderately depressed clients (with Patient Health Questionnaire (PHQ-9) scores between 10 and 20) are offered BA as first-hand treatment, due to its non-invasive nature. Clients who do not respond to BA treatment after four weeks of therapy or who, for extenuating reasons, exhibit worsening depressive symptoms (PHQ-9 > 20) will be offered insurance-paid, guideline antidepressant medication (e.g., Amitriptyline) following standard medication prescription algorithm set by provincial psychiatric hospitals. At the top step, those with severe and treatment-resistant depression (PHQ-9 > 20 without reduction), developing high risk of suicide or other MH comorbidities will be referred to the provincial psychiatric hospital for further clinical evaluation and treatment. This model allows for more effective shifting of depression care tasks from the provincial-level psychiatric hospital, through the District Health Centers, to the local CHSs so that quality primary MH care services become more integrated into the community and readily available for people in need. The effectiveness of this program has been shown previously in an RCT conducted in Vietnam [20]. However, it is not clear what the added value and effectiveness of additional implementation supports, such as enhanced supervision and community-engaged learning collaboratives may be. Therefore, selected CHS will be randomly assigned into 1 of the 3 implementation arms, each of which will receive different levels of implementation support as described below:

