### Outcome evaluation and analysis for AIM 1 (Fidelity to MCCD)

#### Power analysis

We used the pwr package in R software to determine the sample size and estimate power to detect a small eta-squared effect size of 0.025 with an expected intra-class correlation coefficient (ICC) of 0.2. Our primary outcome analyses focus on the 12-month timepoint, we will enroll 10 providers per site resulting a total of 360 providers (180 CHS staff and 180 non-CHS staff) across 36 sites in order to achieve 80% power to detect the small effect size. We also enroll 18 clients per site per phase which results in a total of 648 clients over two phases. With client outcome, power calculations assume near-normal outcomes with a two-sided Type I error of 0.05, this design has 80% power to detect small effects (small Cohen’s d effect size of 0.14 for a 3 × 3 contingency table chi-square test, given 4 degrees of freedom [(3 intervention groups {UI, UI + ES, UI + ES + CELC} − 1)*(3 outcome levels of PHQ-9 score change from baseline to 6 months {positive change, no change, negative change} − 1)]).

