#### Client outcomes

Clients identified with depression as part of routine depression screening at CHS will be recruited to participate in the client outcomes survey study across two implementation support phases. Eligible clients included those who are (1) new to the program, (2) aged 18–65, and (3) screened positive for depression using the PHQ-9 (score > 9). Those with a risk for severe mental illness (psychosis, mania, and substance abuse) will be excluded from the Client Study Cohort and referred to the provincial psychiatric hospital, per the stepped care model mentioned in the intervention description. Based on a depression screening rate of 20% and a research acceptance rate of 75% from our prior work [20], we expect CHS staff to screen 2,200 clients to consent 324 participants across each province for each Client Study Cohort. Across the total sample of 648 clients in each implementation phase. We will request permission from participants to link survey data to client administrative and clinical data.

The effectiveness on the client outcome will be measured based on the client’s improvement (defined as a 50% reduction in PHQ-9 score between the first and last BA session) and client’s remission (defined as the last PHQ-9 score less than 5). We will conduct an intent-to-treat analysis (e.g., those who are lost to follow-up are considered neither improved nor remised) in order to ensure the randomization process. A generalized linear mixed-effects model will be used for binary outcomes with a binominal family distribution and logit link. Exponentiating the fix-effect coefficients for treatment conditions will result in estimates of the odds ratio regarding the effect of treatment condition on depression symptomatology. These models will be adjusted for the clustering effects across multiple levels of hierarchical data structure (e.g., providers, clients) and the UI intervention will be used as a reference group.

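### The client sample is sized on a three-level PHQ-9 change to 6 months, but the stated client models analyse two binary outcomes over the BA sessions, and no proportion worsening is compared by arm

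*Protocol article*

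**What the plan says.** Two sections of the protocol article describe the client PHQ-9 outcome differently.

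- **Power analysis (Aim 1).** The client outcome has "3 outcome levels of PHQ-9 score change from baseline to 6 months {positive change, no change, negative change", crossed with the three arms. The test is a "contingency table chi-square test, given 4 degrees of freedom". The claim is that "this design has 80% power to detect small effects", with an "effect size of 0.14".
- **Client outcomes.** Effectiveness is measured by improvement (PHQ-9 halved between the first and last BA session) and remission (last PHQ-9 below 5). Each is binary and analysed in a logistic mixed model with UI as reference. On missing clients: "those who are lost to follow-up are considered neither improved nor remised".

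Table 1 repeats the binary definitions ("50% reduction in PHQ-9 score" for improvement) and takes both from session scores. Its Effectiveness row also lists PHQ-9 differences before and after treatment. The RE-AIM outcomes section compares the Table 1 indicators by arm with ANOVA or Kruskal-Wallis tests, and the Aim 3 section uses average PHQ-9 as one effectiveness measure. Separately, the stepped-care description makes it a trigger for a change of care when clients "exhibit worsening depressive symptoms (PHQ-9 > 20").

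**The concern.** A sample size statement should describe the outcome that will be analysed. Here the outcome, the time window and the test all differ between sizing and analysis. The worsening level appears in the power section and in no stated client analysis.

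On both binary outcomes, a client whose score falls by 40% without reaching remission, one who is unchanged, one who worsens and one who is lost are all coded as failures. A rise in PHQ-9 after the last BA session but before 6 months cannot change either code.

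This bears on the trial's purpose. UI receives limited technical support before rollout, while ES adds nine months of supervision, and the results are meant to inform scale-up. Whether less support leaves more clients worse off is a natural question for that decision. The article itself treats worsening as clinically important.

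**Working it through.** **1. Reproducing the stated figure.** Inputs from Power analysis: alpha 0.05, power 80%, df = (3 − 1)(3 − 1) = 4, N = 648. The effect size is labelled Cohen's d, but for a contingency table it acts as Cohen's w. Power comes from the noncentral chi-square with noncentrality N·w².

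- The critical value on 4 df is 9.49. Power of 80% needs noncentrality 11.94.
- Detectable w = √(11.94 / 648) = 0.136, which rounds to the stated 0.14.
- At exactly w = 0.14, noncentrality is 648 × 0.0196 = 12.70 and power is 82.7%.
- With 1,296 clients (the Abstract's total), detectable w = √(11.94 / 1,296) = 0.096.

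So 0.14 belongs to 648 clients, the three-level outcome and no clustering. The section describes 648 as the total over two phases, yet 18 × 36 = 648 is one phase.

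**2. Does 0.14 describe the binary endpoints?** A binary outcome by three arms has 2 df and needs noncentrality 9.63. Detectable w = √(9.63 / 648) = 0.122, ignoring clustering. The stated figure therefore does not apply to improvement or remission.

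**3. Clustering.** The power section gives an ICC of 0.2 before the provider numbers and does not visibly use it for clients. With 18 clients per site, the design effect is 1 + 17 × ICC.

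| ICC | Design effect | Effective N | Power at w = 0.14 |
|---|---|---|---|
| 0.01 (assumed) | 1.17 | 554 | 76% |
| 0.05 (assumed) | 1.85 | 350 | 53% |
| 0.2 (stated, if it applied to clients) | 4.4 | 147 | 24% |

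**4. What the binary codes lose.** This is an illustration; the article gives no worsening rate. Take 648 / 3 = 216 clients per arm in one phase, with 50% improved and 30% remitted in two arms, and 5% versus 15% worsened. That is 0.05 × 216 ≈ 11 versus 0.15 × 216 ≈ 32 clients. The odds are 0.5/0.5 in both arms for improvement and 0.3/0.7 in both for remission, so both odds ratios are 1.0. This follows from assuming equal improvement and remission. It shows that those models cannot separate the remaining categories.

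**5. Would the mean comparison show it?** Assume the extra 10% of clients worsen by 5 points instead of staying unchanged, with an SD of change of 5 to 6.

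- Mean shift: 0.10 × 5 = 0.5 points, so d = 0.5/5 = 0.10 or 0.5/6 = 0.083.
- Noncentrality d·√(216/2) = 1.04 or 0.87, giving pairwise power of about 18% or 14%.
- Direct comparison: SE = √[(0.05 × 0.95 + 0.15 × 0.85) / 216] = 0.0285. Then 0.10 / 0.0285 − 1.96 = 1.55, so power is about 94%.
- With the design effect of 4.4, divide each standardised difference by √4.4 = 2.10. Power falls to about 7 to 8% for the mean and 39% for the direct comparison. The contrast remains, but neither is strong.

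**The case against.** The strongest reply is that worsening is already in the analysis. Table 1 lists pre/post PHQ-9 differences, the RE-AIM outcomes section compares indicators by arm, and the cost-effectiveness analysis uses average PHQ-9 and QALYs. Signed change, increases included, therefore enters an arm comparison, and an arm with more worsening would be penalised. This stands. A reader might infer from the Client outcomes section that worsening is never compared, or that a difference in harm would be invisible. The documents do not support that. What is absent is a comparison of the proportion worsening, and step 5 shows why a mean is a weak substitute.

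A second reply is that the chi-square in the power section is itself a comparison of arms that includes negative change. It is described there only as the basis of the power calculation, and the section on client analysis does not take it up.

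A third reply is that a condensed article leaves secondary categories and safety tables to a full protocol or SAP. That would answer a bare request for a deterioration outcome. It does not answer two sections of the same article naming different outcomes, windows and tests.

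Two further limits stand. The 5% and 15% rates are assumed. A reader might also take the treatment to be lay-delivered, but the article describes CHS providers as usually physician assistants or nurses, and gives non-CHS staff outreach, PHQ-4 screening and referral.

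**Conclusion.** The point holds as an inconsistency between the Power analysis and Client outcomes sections. The three-level change to 6 months has no matching stated analysis. The 0.14 at 80% power describes that outcome with 648 clients and no clustering, not improvement or remission. The two binary outcomes merge worsened, unchanged and lost clients. Mean or rank change is compared by arm; a proportion worsening is not.

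The power contrast of about 14 to 18% versus 94% rests on assumed rates, a 5-point worsening, an SD of 5 to 6, 216 clients per arm and independence. It shows why the category matters and does not predict this trial's results. The mismatch concerns the client sample only: providers are sized separately, on an eta-squared of 0.025.

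**What to change.** - Reconcile the Power analysis and Client outcomes sections so that outcome, window and test agree, or state why they differ.
- Report the three-level PHQ-9 change from baseline to 6 months by arm, from the PHQ-9 already collected. Pre-state the margin that counts as no change; the article gives none, and without one a one-point rise would count as negative.
- Estimate the proportion with negative change by arm, with confidence intervals, in the mixed-model family already planned for improvement and remission, with clustering included.
- Show clients lost to follow-up as a separate category, merged with neither unchanged nor worsened.
- Label this analysis descriptive, with no added claim of success.
- State that 0.14 at 80% power refers to the three-level outcome without clustering, and not to the binary endpoints.

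The cost is one outcome definition and one further model, with no new visits. Intervals will be wide, because worsening is likely to be uncommon and clients are clustered. In the 5% versus 15% illustration, the 95% half-width for the difference is 1.96 × 0.0285 = 5.6 percentage points without clustering. It is about 11.7 points (5.6 × 2.10) if the ICC of 0.2 applied to clients.

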#### RE-AIM outcomes

According to the RE-AIM framework, for an intervention to have an impact, it must **Reach** the population in need of the service, demonstrate **Effectiveness**, be **Adopted** by the system and providers, be **Implemented** with quality, and be **Maintained** or sustained over time. The indicators’ description as well as data sources were presented in detail in Table 1. A cascade of MH care will be built based on these indicators (Fig. 2). Mean and standard deviation will be presented without the normality violation, otherwise, median and interquartile ranges will be used. Independent ANOVA and/or Kruskal-Wallis test will be applied to assess differences stratified by intervention arms.

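### Client effectiveness is modelled only as two yes/no cuts of PHQ-9, and the uncut score gets no stated clustered, baseline-adjusted analysis; the power lost depends strongly on the intracluster correlation and the client total

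*Protocol article*

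**What the plan says.** In the Client outcomes section, effectiveness is measured by "client’s improvement (defined as a 50% reduction in PHQ-9 score between the first and last BA session) and client’s remission", the latter meaning a last PHQ-9 below 5. Clients lost to follow-up count as failures on both. The model is then fixed: "A generalized linear mixed-effects model will be used for binary outcomes with a binominal family distribution and logit link". It is said to adjust for clustering, with UI as the reference arm.

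The Power analysis section takes a different view of the same instrument: "power calculations assume near-normal outcomes with a two-sided Type I error of 0.05". It then sizes a "contingency table chi-square test, given 4 degrees of freedom" on PHQ-9 change from baseline to 6 months in three levels (positive, none, negative), with an "effect size of 0.14 for a" 3 × 3 table, and says that "this design has 80% power to detect small effects".

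The uncut score appears in two other places. The Effectiveness row of Table 1 lists "Pre- and post-treatment differences; PHQ-9 Survey data", and the RE-AIM outcomes section gives a general rule for indicators: "Independent ANOVA and/or Kruskal-Wallis test will be applied to assess differences stratified by intervention arms". Aim 3 uses average PHQ-9 as one effectiveness input to the ICER.

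**The concern.** PHQ-9 runs from 0 to 27 and is recorded repeatedly. A 50% cut treats a fall from 20 to 11 as equal to no change, and separates it from a fall from 20 to 10. The article gives no reason for making the cuts the modelled form.

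The trial looks for small differences between three active support strategies with 36 randomised sites, so information is scarce. If a real ES or CELC benefit is a modest shift in severity, a cut is less likely to show it. A null client result could then reflect the scale of analysis and not the strategies. The effectiveness result would also rest on a different client effect from the average PHQ-9 used in Aim 3.

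**Working it through.** **Inputs from the article.** Two-sided alpha 0.05; 80% power; effect size 0.14; 3 × 3 table, 4 df; 36 CHSs in three equal arms; 18 clients per CHS per phase. The client total is 648 in the Power analysis section. It is 648 per phase in the Client outcomes section, and 1,296 in the abstract. An ICC of 0.2 opens the power paragraph, but whether it covers clients is not said.

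**Assumptions, not in the article.** Event rates of 20%, 30% and 50%; client ICC from 0 to 0.20; each outcome a single cut of a normal score that shifts between arms; the three sizing categories equal thirds.

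**1. Reproduce the plan's figure.** The non-centrality giving 80% power on 4 df at 0.05 is 11.94. With 648 clients, w = √(11.94/648) = 0.136, which rounds to the stated 0.14. So 0.14 acts as Cohen's w, for 648 clients, with no allowance for clustering. With 1,296 clients, w would be 0.096.

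**2. Information kept by a cut.** For event rate p with normal cut point c, the share kept is φ(c)²/[p(1−p)].
- p = 0.5: 0.3989²/0.25 = 0.637
- p = 0.3: 0.3477²/0.21 = 0.576
- p = 0.2: 0.2800²/0.16 = 0.490

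The loss is 36%, 42% and 51%.

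**3. Power with 648 independent clients.** Equal thirds keep 2 × 0.3636²/(1/3) = 0.793. The full-score non-centrality is 11.94/0.793 = 15.05, which gives 94.5% power on 2 df. Multiplying 15.05 by 0.637, 0.576 and 0.490 gives 9.58, 8.66 and 7.37, and power of 79.8%, 75.4% and 68.0%. The loss is 14.7, 19.1 and 26.5 points.

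**4. Clustering.** Divide the full-score non-centrality by 1 + (m−1)ICC, and the cut's by the same expression with the ICC of the cut variable, derived from the bivariate normal. For example, at ICC 0.20 and m = 18:
- Full score: 15.05/(1 + 17 × 0.20) = 15.05/4.40 = 3.42.
- Cut at 50%: its ICC is (2/π)·arcsin(0.20) = 0.128, so 9.58/(1 + 17 × 0.128) = 9.58/3.18 = 3.01.

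The rows for 1,296 clients double the non-centrality and use m = 36, with the same effect per client.

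| Clients | ICC | Full score | Cut, 50% rate | Cut, 30% rate | Loss (points) |
|---|---|---|---|---|---|
| 648 | 0 | 94.5% | 79.8% | 75.4% | 14.7-19.1 |
| 648 | 0.02 | 86.0% | 71.0% | 67.1% | 15.0-18.9 |
| 648 | 0.05 | 72.5% | 60.0% | 56.9% | 12.5-15.6 |
| 648 | 0.10 | 55.1% | 46.9% | 44.7% | 8.2-10.4 |
| 648 | 0.20 | 36.1% | 32.3% | 30.9% | 3.9-5.2 |
| 1,296 | 0 | 99.9% | 98.1% | 96.9% | 1.8-3.0 |
| 1,296 | 0.05 | 85.1% | 77.4% | 75.0% | 7.7-10.0 |
| 1,296 | 0.10 | 63.4% | 57.9% | 56.0% | 5.6-7.4 |
| 1,296 | 0.20 | 39.3% | 36.8% | 35.6% | 2.5-3.8 |

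At ICC 0.20 with 18 per CHS, the information lost to the cut is 12-23% over event rates of 50% to 20%.

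**5. Sensitivity to the three-level split.** For unequal splits, the unclustered loss with 648 clients at 50% and 30% event rates is 9-17 points. For an 80/10/10 split it is 5-8.

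**6. Simulation on an assumed scenario.** 36 CHSs of 18 clients, SD 5, baseline correlation 0.4, UI-to-CELC shift 0.4 SD, CHS-level F-test, 1,500 runs.
- ICC 0.02: improvement 0.77-0.79, remission 0.73-0.75, full score 0.88-0.89, baseline-adjusted score 0.92.
- ICC 0.05: improvement 0.69, remission 0.63-0.65, full score 0.76-0.77, baseline-adjusted score 0.80-0.82.

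**The case against.** **The power loss is not the plan's own.** A reader might infer that the article's sizing implies a loss of 15-26 points. It does not. That range needs equal thirds, assumed event rates, independent clients and the lower of two client totals. Clients enter with PHQ-9 above 9 and are then treated, so a mostly positive split is more plausible than equal thirds. If the ICC of 0.2 applies to clients, the loss is 4-5 points. This objection stands, and the size is stated conditionally for that reason.

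**A 50% reduction is a ratio, not one cut.** In the simulation at ICC 0.05, improvement loses 7-8 points against the unadjusted score, where the formula gives 13-16. Counting losses to follow-up as failures is not in the formula either. This stands: the formula figures are approximate, and for improvement may be too large.

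**The article may simply be condensed.** A reader might infer that the full score is never analysed. Table 1, the general ANOVA/Kruskal-Wallis rule and Aim 3 show otherwise, and a fuller plan may hold more. This stands against any claim that the score goes unused. It does not remove the point, because the article itself fixes the cuts and their model, and the test it gives that could reach the uncut difference is described without clustering or baseline adjustment.

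**Improvement and remission are declared RE-AIM indicators**, and the trial's main focus is provider adoption and implementation quality. This also stands, and is why the binary outcomes should be kept.

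**Conclusion.** The point holds in a limited form. The only model stated for client effectiveness uses PHQ-9 as two cuts, while the plan assumes near-normality and sizes on change to 6 months. No clustered, baseline-adjusted analysis of the score is stated. Under independence and assumed event rates of 20-50%, a cut loses about 36-51% of the information.

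In every setting computed the cut has less power, but the amount varies. With 648 clients and event rates of 50% and 30%, it is about 15-19 points at ICC 0.02, 13-16 at 0.05, 8-10 at 0.10 and 4-5 at 0.20. With 1,296 clients at ICC 0.20 it is about 2-4. The article does not say which setting applies, because it gives no event rates and no ICC tied to clients, and its client totals disagree. The change is worth making because the scores are already collected, but the case does not rest on one headline power figure.

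**What to change.** In the Client outcomes section, add as the main comparison of PHQ-9 severity a linear mixed model of the follow-up score. Use arm as fixed effect, baseline PHQ-9 as covariate and a random intercept for CHS, and report adjusted mean differences with 95% confidence intervals. If the scores are clearly non-normal, use a proportional-odds mixed model. For this outcome it replaces the unclustered ANOVA/Kruskal-Wallis. Include all randomised clusters and all available scores under a stated missing-at-random assumption.

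Keep improvement and remission as the declared responder indicators, with their logistic mixed model and the rule that loss counts as failure.

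Say which follow-up score is meant. In the Power analysis section, restate client power for this clustered analysis as a mean difference in PHQ-9 points, with the client ICC and one client total.

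No extra visits, clients or staff are needed, but there are costs. A mean difference is less familiar to policymakers than a percentage improved, which the retained indicators cover. If the 6-month survey score is used instead of the last BA-session score, the time point, the data source and possibly the population differ from the session-based outcomes. The handling of missing scores also differs from the binary analyses. The text should say so.

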**Methods:**

In this cluster-randomized controlled trial, CHSs will be randomly assigned to one of three implementation conditions: (1) Usual Implementation (UI), which consists of training workshops and toolkits; (2) Enhanced Supervision (ES), which includes UI combined with bi-weekly/monthly supervision; and (3) Community-Engaged Learning Collaborative (CELC), which includes all components of ES, combined with bi-monthly province-wide learning collaborative meetings, during which cross-site learning and continuous quality improvement (QI) strategies are implemented to achieve better implementation outcomes. The primary outcome will be measured based on the RE-AIM framework (Reach, Effectiveness, Adoption, Implementation quality, and Maintenance) using indicators on implementation, provider, and client factors. The secondary outcome examines factors associated with barriers and facilitators of quality implementation, while the tertiary outcome evaluates the incremental cost-effectiveness ratio of services provided in the ES and CELC conditions, relative to UI condition for depression care. A total of 1,296 clients receiving depression care at CHSs will be surveyed at baseline and 6-month follow-up to assess mental health and psychosocial outcomes (e.g., depression and anxiety severity, health function, quality of life). Additionally, 180 CHS staff and 180 non-CHS staff will complete pre- and post-training evaluation and surveys at baseline, 6, 12, and 24 months.

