### Study site eligibility and recruitment

We are recruiting 36 community health stations (CHSs) from two provinces (Bac Giang and Phu Tho) that are located within a one-to two-hour drive from Hanoi capital. CHSs from each province will be randomly assigned into one of three intervention conditions with two implementation support phases: Phase 1—Active Implementation Support, and Phase 2—Sustainable Support (e.g., after supervision is withdrawn from the international training team and transitioned to the local supervision team). The recruitment process involves (1) identifying three potential districts per province based on recommendations from the provincial health department and psychiatric hospital, (2) conducting engagement meetings with three district-level health leaders to introduce the project and expectations, (3) conducting engagement meetings with CHS leaders to introduce the program, and (4) inviting interested CHS administrators to submit a form indicating interest in participating, as well as willingness to be randomized, and to complete a brief CHS assessment survey.

CHS selection criteria include having at least one physician/physician assistant, ≥ 5 CHS staff, ≥ 5 non-CHS staff including health collaborators/Village health workers (VHWs), serving a population of at least 5,000, and of which, ≥ 200 clients visit CHS monthly. We will score CHSs based on two main categories: (1) *site characteristics* (e.g., distance to district health centers and provincial psychiatric hospital, staff-to-client ratio, number of clients per month); and (2) *MH indicators* (e.g., implementing any MH programs, management and treatment for schizophrenia and epilepsy clients, accessibility to psychotropic medications). Given the total summary scores, CHSs will be classified as high- and low-performing sites. We will use Statistical Analysis Software (SAS) version 9.4 to randomly assign CHSs within a province into one of three conditions and the randomization process occurs within matched sites within district level, resulting in 6 UI, 6 ES, and 6 CELC. Each intervention arm will include 3 high performers and 3 low performers. Due to cost and staffing, we are implementing intervention at 18 CHSs in Bac Giang in the first year (2022) and will be continuing at 18 CHSs in Phu Tho in February, 2023.

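### The clustering sentence for the client model names providers and clients but not the CHS, which is randomised; fitted with those levels only, arm contrasts would have standard errors that are too small

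*Protocol article*

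**What the plan says.** The abstract fixes the design: "In this cluster-randomized controlled trial, CHSs will be randomly assigned to one of three implementation conditions". Study site eligibility and recruitment adds that, in each province, "the randomization process occurs within matched sites within district level, resulting in 6 UI, 6 ES, and 6 CELC", and that "Each intervention arm will include 3 high performers and 3 low performers".

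The client model is described under Client outcomes: "A generalized linear mixed-effects model will be used for binary outcomes with a binominal family distribution and logit link". Improvement is "defined as a 50% reduction in PHQ-9 score between the first and last BA session" and remission is a last PHQ-9 below 5, so each client contributes one value to each outcome. Usual implementation is the reference arm, and the models are to be "adjusted for the clustering effects across multiple levels of hierarchical data structure (e.g., providers, clients", given as examples. The section lists no covariates.

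No other analysis text supplies the CHS level. RE-AIM outcomes plans ANOVA or Kruskal-Wallis comparisons by arm and does not mention clustering. Power analysis states an ICC of 0.2 next to the provider calculation and gives no separate ICC for clients.

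**The concern.** In a cluster-randomised trial the arm effect is estimated between clusters, so the variation between CHSs has to enter its standard error. The sentence that states the clustering levels gives two, and neither is the CHS. One of them, the client, has no within-unit replication for a single binary outcome, so its random intercept cannot be estimated.

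An analyst who follows the named levels is left with a provider intercept. That treats providers at the same CHS as independent and spreads the CHS variance over several providers. Intervals for ES against UI and CELC against UI would be too narrow, and a false claim of superiority too likely.

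A lesser matter is that the section does not say whether the factors used in the restricted randomisation, or baseline PHQ-9, enter the model.

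**Working it through.** **1. The plan's own client figure.** Inputs (Power analysis): 80% power, effect size 0.14, 3 × 3 chi-square with 4 df, alpha 0.05, 648 clients. Using a non-central chi-square with non-centrality N·w², 80% power at N = 648 needs w = 0.136, which rounds to 0.14. (w = 0.14 exactly gives 82.7%.) The figure therefore reproduces only with 648 independent clients. With 18 clients per CHS and ICC 0.2, the design effect is 1 + 17 × 0.2 = 4.4, the effective N is 648/4.4 = 147, and power at w = 0.14 is about 24%. So the power statement does not show that CHS clustering was carried into the client analysis.

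**2. Variance under a provider-only model.** From the document: 36 CHSs, 12 per arm (6 per arm in each of two provinces); 18 clients per CHS in one phase; 5 CHS staff providers per CHS. Assumed: clients are spread evenly, 18/5 = 3.6 per provider; total ICC ρ is 0.05, 0.1 or 0.2; a share s of the clustering lies at CHS level and the rest at provider level.

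- True design effect: 1 + (3.6 − 1)ρ + (18 − 3.6)sρ
- Provider-only design effect: 1 + (3.6 − 1)ρ
- SE ratio R = √(true / provider-only)
- Type I error = 2[1 − Φ(1.96/R)]

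Example, ρ = 0.2 and s = 0.25: true = 1 + 0.52 + 0.72 = 2.24; provider-only = 1.52; R = 1.21; type I error 10.6%.

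**3. Simulation check.** Null binary data with success probability 0.4, one contrast of 12 against 12 CHSs, 18 clients per CHS as 6 providers × 3 clients (assumed), ICC on the latent logit scale, 4,000 runs per setting. Provider means (t, 142 df) were compared with CHS means (t, 22 df). This stands in for the mixed model and is not a fit of it. Monte Carlo error near 5% is √(0.05 × 0.95/4000), about 0.3 points.

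| ICC | CHS share | True / provider-only design effect | SE ratio | Type I, formula | Type I, simulated, provider only | Type I, simulated, CHS |
|---|---|---|---|---|---|---|
| 0.05 | 25% | 1.31 / 1.13 | 1.08 | 6.9% | 7.4% | 5.5% |
| 0.05 | 100% | 1.85 / 1.13 | 1.28 | 12.6% | 11.8% | 5.3% |
| 0.1 | 25% | 1.62 / 1.26 | 1.13 | 8.4% | 7.7% | 5.4% |
| 0.1 | 100% | 2.70 / 1.26 | 1.46 | 18.1% | 16.0% | 4.7% |
| 0.2 | 25% | 2.24 / 1.52 | 1.21 | 10.6% | 10.1% | 4.9% |
| 0.2 | 50% | 2.96 / 1.52 | 1.40 | 16.0% | 15.0% | 5.2% |
| 0.2 | 75% | 3.68 / 1.52 | 1.56 | 20.8% | 18.5% | 5.3% |
| 0.2 | 100% | 4.40 / 1.52 | 1.70 | 24.9% | 25.0% | 4.8% |

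**4. Sensitivity to the number of providers.** With 3 providers × 6 clients per CHS and all clustering at CHS level, the arm-mean variance is ICC/12 + (1 − ICC)/216, against ICC/36 + (1 − ICC)/216 under provider only. ICC 0.2: 0.02037 against 0.00926, ratio 2.20, type I error 19%. ICC 0.05: 0.00857 against 0.00579, ratio 1.48, type I error 11%. Fewer providers reduce the error but do not remove it.

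**5. Randomisation factors.** If they explain a share q of the CHS variance, the variance ratio after adjustment is [ICC(1 − q) + (1 − ICC)/18] / [ICC + (1 − ICC)/18]. For q = 0.2 to 0.4 (assumed), ICC 0.2 gives 0.204/0.244 to 0.164/0.244, so intervals are 9% to 18% shorter. ICC 0.05 gives 0.0928/0.1028 to 0.0828/0.1028, so 5% to 10% shorter. This is a linear approximation.

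**The case against.** The parenthesis is introduced as examples, so the list is open, and no sentence excludes a CHS effect. A text that promises adjustment at several levels, in an article that states an ICC of 0.2 and enrols by site, may well intend the CHS as the top level. Clients may be named only as the lowest layer of the data and not as a random intercept. This stands, and it makes the error conditional. It does not make the sentence adequate, because the level that must be modelled is the one left unnamed and nothing elsewhere in the analysis text supplies it.

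The type I figures depend on a split of the clustering between CHS and provider that the document does not give. That also stands, which is why a range is shown. Even at a quarter of the clustering at CHS level, the error at ICC 0.2 is about double the nominal 5%.

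A reader might go further and infer that the plan is wrong to leave out the randomisation factors and baseline PHQ-9. The document does not support that. It lists no covariates at all, and an article commonly leaves them to the analysis plan. Leaving out matched strata usually makes standard errors too large, the opposite direction from leaving out the CHS.

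Nor would baseline PHQ-9 protect against recruitment bias in general. It adjusts for measured severity only, and improvement is already relative to the first-session score, so the gain is mainly for remission. That clients enter after randomisation is itself an inference: "Clients identified with depression as part of routine depression screening at CHS will be recruited", while only providers are said to be recruited beforehand.

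**Conclusion.** The clustering sentence for the client model should be corrected. It names a level that cannot be used for a single binary outcome and does not name the randomised unit. If the named levels alone are fitted, the true standard error of an arm contrast is 1.21 to 1.70 times the reported one at ICC 0.2. The type I error is then about 10% to 25% at ICC 0.2, 8% to 16% at 0.1 and 7% to 12% at 0.05 (simulated), against about 5% with the CHS as the cluster.

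These figures assume 3 to 4 clients per provider, 18 clients per CHS, 25% to 100% of the clustering at CHS level, and that the stated ICC of 0.2 is a fair upper value for clients.

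A reader might infer that the trial will report wrong standard errors. The document does not show that; it shows a specification that permits them. The absence of strata and baseline PHQ-9 is not a defect of this document, only an opportunity to gain precision.

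**What to change.** Replace the parenthesis under Client outcomes with an explicit structure: a random intercept for CHS, provider nested within CHS if estimable, and no client-level random effect for improvement or remission. State a small-sample correction for 36 clusters, for example a t reference on between-cluster degrees of freedom.

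As a secondary step, add fixed effects for the factors used in randomisation, where "the randomization process occurs within matched sites within district level": district, which already contains province, and high or low performance. Add baseline PHQ-9 as a continuous covariate, chiefly for remission.

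The cost is analysis wording. The CHS, its district and its performance class are known from randomisation, and every client has an entry PHQ-9. If three districts per province take part, district uses 5 and performance class 1 of the 36 − 3 = 33 between-CHS degrees of freedom, leaving 27. If the matched sets are triplets (assumed), adjusting for the 12 sets instead would use 11 and leave 22. Intervals will be wider than under a provider-only model, as they should be.
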